#### Continuous variables

If the data shows a normal distribution, the data will be expressed as the mean ± standard deviation. Differences between groups are analysed by one-way ANOVA. If the data does not show a normal distribution, the data will be expressed as the median, lower 25% quantile, and upper 75% quantile. Differences between groups are analysed by the Kruskal-Wallis *H* test and the Nemenyi test.

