### Outcomes {12}

#### Primary outcomes

Primary outcomes are as follows:
The proportion of patients with relief of leukopenia and/or neutropenia.The number and proportion of patients with relief of myelosuppression-associated SAE, defined as grade 3–4 leukopenia and/or neutropenia and FN.The median and mean duration time of relief of leukopenia and/or neutropenia.The dosing of rhG-CSF.

The grading of adverse reactions is in accordance with the CTCAE 4.0.2 criteria. Leukopenia is defined as an abnormal decrease in white blood cells of less than LLN-3.0 × 10^9^/L. Neutropenia is defined as an abnormal decrease in netrophils of less than LLN-1.5 × 10^9^/L. The definition of FN is based on the IDSA guidelines (American Society of Infectious Diseases Guide 2010 edition), which is an absolute neutrophil count (ANC) of < 500 neutrophils/mcL or an anticipated decline to ≤ 500 in the next 48 h and progress to ≥ 38.3 °C orally or ≥ 38.0 °C for a duration over 1 h.

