### Sample size {14}

In previous studies, the incidence rate of myelosuppression was 81.0% in the control group and 61.7% in the TCM decoction group [29]. The cure rate and effective rate of the moxibustion group were 84.1% and 66.4%, while those of the control group were 35.2% and 33.3% [30]. In our preliminary study, the bone marrow suppression rate (grade 2 or above) was 52% and 81% for the MD group and the control group, respectively (δ = 15%in superiority trial). Since there are no previous data supporting the combination use of moxibustion and TCM decoction, the sample size calculation was simply based on MD/MP group versus control group, assuming that the effect of combination treatment is equivalent to or better than moxibustion or decoction alone. Considering patient enrolment at a ratio of 1:1:1 for the control, MD, and MP groups, the sample size is calculated by multiple sample rate comparisons. The sample content estimation formula is as previously described [31]. Given that *α* = 0.05 and 1-*β* = 0.08, taking a 20% drop rate into account, the required total sample size is 462 cases and 154 cases in each group.

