## Statistical methods

### Statistical methods for primary and secondary outcomes {20a}

Data were analysed using SPSS 18.0 (SPSS, lnc., Chicago, IL) and Stata10.0 (StataCorp, College Station, Texas). Multivariate analysis was performed by multiple linear regression, COX regression, or logistic regression, where appropriate. All analyses are based on two-sided test, with *P* values < 0.05 considered as statistically significant.

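### Optional efficiency gain: with three arms, a written Kruskal-Wallis gate followed by two-arm rank-sum tests controls family-wise error as Nemenyi does, with more power for MD versus MP

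*Protocol article*

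**What the plan says.** Under Continuous variables, the method depends on the observed distribution. Normal data go to one-way ANOVA. Otherwise: "If the data does not show a normal distribution, the data will be expressed as the median, lower 25% quantile, and upper 75% quantile", and the arms are compared by the Kruskal-Wallis H "test and the Nemenyi test". The two tests are joined by a plain conjunction. The text does not say that Nemenyi is run only after a significant Kruskal-Wallis result, and it does not say which form of Nemenyi is meant.

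The general rule in Statistical methods {20a} is: "All analyses are based on two-sided test, with *P* values < 0.05 considered as statistically significant".

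The primary outcomes in Outcomes {12} include "The dosing of rhG-CSF" and the duration of relief of leukopenia or neutropenia, the latter to be given as both median and mean. No standard deviation, distribution or expected difference is stated for either.

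Sample size {14} plans a 1:1:1 allocation and concludes that "the required total sample size is 462 cases and 154 cases in each group", "taking a 20% drop rate into account". It rests on a binary rate: "the bone marrow suppression rate (grade 2 or above) was 52% and 81% for the MD group and the control group". The comparison sized is MD/MP against control. MD against MP has no stated effect and no stated power.

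**The concern.** Nemenyi compares all pairs of arms and pays for it twice. It raises the pairwise critical value from 1.96 to 2.34 (2.45 in the chi-square form). It also ranks the three arms together, so the MD versus MP comparison depends on the control data and its standard error grows when control lies apart from the other two.

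With three arms that price can be avoided. The hypotheses are the three pairwise nulls and their intersections, and any two pairwise nulls together already imply that all three arms are equal. The only intersection to test is therefore the global null, which is what Kruskal-Wallis tests. If it is rejected at 0.05, each pair can be tested at 0.05 and the family-wise error stays at 5% by closed testing.

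What is at stake is power on the two smaller contrasts, MD versus MP and MP versus control. MD versus MP is the only placebo-controlled contrast in the trial.

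**Working it through.** **The plan's own figure.** Superiority by a 15-point margin, with 81% against 52%: n = [0.81×0.19 + 0.52×0.48] × (1.645 + 0.842)² / (0.29 − 0.15)² = 0.4035 × 6.18 / 0.0196 = 127.3, so 128 per arm. Then 128 × 1.2 = 153.6, so 154 per arm and 462 in total. This takes the printed power as 0.80 and needs one-sided 0.05. Nothing below depends on that. With 20% dropout, 154 × 0.8 = 123 per arm remain.

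**Critical values for one pair among three arms.** Unadjusted 1.960. Nemenyi by the studentized range: 3.314/√2 = 2.344. Nemenyi in chi-square form: √5.991 = 2.448.

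**Family-wise error** (simulation, 10,000 trials, 123 per arm, normal shifts):

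| True state | Gated Wilcoxon | Kruskal-Wallis + Nemenyi | Ungated Wilcoxon |
|---|---|---|---|
| All arms equal | 5.3% | 4.7% | 13.1% |
| One arm 0.7 SD away | 5.3% | 1.7% | 5.3% |
| One arm 1.5 SD away | 5.0% | 0.7% | 5.0% |

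The gated procedure holds 5% within simulation error. Nemenyi spends much less when one arm differs.

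**Power, zero-inflated dose model** (5,000 trials per scenario). Dose is 0 with probability 1 − p, otherwise gamma (mean 10 units, CV 0.8) rounded up, with the same distribution among users in every arm. From Sample size {14}: p = 81% for control and 52% for MD. Assumed: that these myelosuppression rates stand for rhG-CSF use, the gamma shape, and the MP rate. For MP, 61.7% is borrowed from a decoction group of an earlier study; 66.5% is the midpoint, (52 + 81)/2. Nemenyi is tie-corrected.

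| n per arm | MP rate | Contrast | Nemenyi | Gated Wilcoxon |
|---|---|---|---|---|
| 154 | 61.7% | MD v MP | 20.3% | 33.0% |
| 154 | 61.7% | MP v control | 74.7% | 83.8% |
| 154 | 61.7% | MD v control | 98.3% | 98.6% |
| 123 | 61.7% | MD v MP | 16.3% | 27.8% |
| 123 | 61.7% | MP v control | 63.4% | 75.4% |
| 154 | 66.5% | MD v MP | 46.4% | 62.4% |

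A separate run of 4,000 trials at 154 per arm varied only the MP rate. MD versus MP was 6% v 12% at 57%, 46% v 63% at 66.5% and 88% v 95% at 75%.

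**Power, simple shift model.** Noncentrality = d × √(n/2) × √(3/π). For d = 0.2 SD and n = 123: 0.2 × 7.842 × 0.977 = 1.533. Power is Φ(1.533 − 1.960) = 33.5% unadjusted and Φ(1.533 − 2.344) = 20.9% with Nemenyi. For other shifts at 123 per arm:

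| Shift | Unadjusted | Nemenyi (2.344) | Loss, points |
|---|---|---|---|
| 0.1 SD | 12.0% | 5.8% | 6 |
| 0.3 SD | 63.3% | 48.2% | 15 |
| 0.4 SD | 86.6% | 76.5% | 10 |
| 0.5 SD | 96.9% | 93.2% | 4 |

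At 154 per arm, 0.2 SD gives 40.3% against 26.5%. The formula ignores the gate, so the least favourable case was simulated: with control equal to MP and MD 0.2 SD away (123 per arm), the gated test has 25.2% and Kruskal-Wallis with Nemenyi 20.3%. The gain shrinks but does not reverse.

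**The case against.** The strongest reply is that nothing here is wrong. The plan names a recognised omnibus test and a recognised all-pairs test that controls family-wise error. With several primary outcomes, some conservatism can be defended. This stands: the point is about efficiency only.

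Four stronger readings are tempting, and the documents do not support them.

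- *A reader might infer that the trial loses power from 33% to 20%.* Those figures belong to one scenario. The article gives no MP rate and no dose distribution, and 61.7% comes from patients on decoction, whereas MP receives placebo. The shift model also gives about 33% and 20%, but at 0.2 SD and 123 per arm; at 154 per arm it gives 40% and 27%, so the agreement is coincidence.
- *A reader might infer that rhG-CSF dose and duration will take this route because of many zeros.* The rhG-CSF section does tie therapeutic use to grade 2 or above. But it also describes prophylactic use for high-risk regimens, and Trial design {8} expects all participants to receive rhG-CSF. Duration of relief may be defined only in affected patients. Skewness is plausible, but the route depends on the data.
- *A reader might infer that Nemenyi is redundant as the text stands.* It is redundant only behind a formal gate, which the text does not state. Without one, Nemenyi is the only family-wise protection for the pairs.
- *A reader might infer a defect because ANOVA and chi-square have no named pairwise method.* That is detail for an analysis plan, which is not shown.

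It is also fair that MD versus MP was never sized and, at an MP rate of 61.7%, stays weak at 33% after the change. This limits the benefit but does not remove it.

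**Conclusion.** A costless improvement, not an error. For three arms, a Kruskal-Wallis gate with two-arm rank-sum tests at 0.05 keeps family-wise error at about 5% within an outcome and had more power than Nemenyi for MD versus MP in every scenario tried. The loss under Nemenyi is roughly 4 to 17 points, depending on the assumed MP rate or shift, the dose distribution and the number evaluable. MP versus control loses about 9 to 12 points in the dose model with MP at 61.7%. MD versus control is practically unaffected. The closed-testing argument needs no assumption about effect size; all the power figures do. The control is within one outcome and does not address multiplicity across the primary outcomes.

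**What to change.** Under Continuous variables, replace the Nemenyi clause with wording to this effect: for non-normal data the three arms are first compared by the Kruskal-Wallis test at two-sided 0.05; only if it is significant is each pair compared by a Wilcoxon rank-sum test at two-sided 0.05, using the data of those two arms alone; the adjusted P value for a pair is the larger of the Kruskal-Wallis and the pairwise P values.

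The gate has to be written as a condition. Dropping Nemenyi without it would leave unadjusted tests with a family-wise error of about 13% when all arms are equal.

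The cost is one sentence, settled before the data are analysed, with no new data and no change in sample size. All that is given up is simultaneous confidence intervals, which the article does not mention.

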#### Categorical variables

The frequency, relative number, and rate of the data will be calculated. If the data is not in order, the chi-square test or Fisher’s exact test is used to compare the difference between groups. If the data is in order, the rank-sum test is used instead.

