## Trial design {8}

This study is a randomized controlled clinical trial single-blinded for TCM decoction but not moxibustion. Patients will be divided into groups by stratified randomized grouping. The stratification factors involve age (below 40s, 40s, 50s, 60s, or above), chemotherapy regimen (anthracyclines, taxanes, anthracyclines combined with taxane, and others), and chemotherapy strategy (adjuvant and neoadjuvant). All eligible patients are equally divided into the control group with no TCM decoction/moxibustion treatment (control), the TCM decoction combined with moxibustion group (MD), and the placebo combined with moxibustion group (MP). All participants are expected to treat with standard chemotherapy and rhG-CSF regimen. The detailed study flow is illustrated in Fig. 1. The clinical pathway of each participant is shown in supplementary figure 1. Patients or the public will not be involved in the design, or conduct, or reporting, or dissemination plans of our research.

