#### rhG-CSF

The rhG-CSF is performed according to the guidelines [12–14]. Patients with grade 1 myelosuppression according to the CTCAE 4.0.2 criteria are follow-up for both the intervention group and the control group. Patients with grade 2 or above myelosuppression should receive rhG-CSF treatment until the WBC count and ANC return normal. Two types of adjuvant chemotherapy regimens in breast cancer, namely ddAC-wP and TAC, can lead to a high risk of FN (incidence > 20%). According to the NCCN guidelines, prophylactic rhG-CSF treatment is recommended on day 2 or days 3 to 4 after chemotherapy. In detail, 5 mcg/kg is administrated per day until neutrophil count returns normal or nearly normal level, or long-acting rhG-CSF (PEG-rhG-CSF) is given on the second day after chemotherapy.

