#### Secondary outcomes

Secondary outcomes are as follows:
Chemotherapy adherence: The percentage of patients who completed the full-course chemotherapy in a standard dose. If only the full course of treatment is completed but the dose of chemotherapy is reduced, or the dose is unchanged but the course of treatment is shortened, the case will be treated as poor adherence.Stratified analysis: Subgroup analysis will be done according to age, chemotherapy regimen, and chemotherapy strategy.Adverse events: Any toxic side effects such as general condition, gastrointestinal reactions, liver and kidney function, skin reactions, burns, and heat syndrome will be recorded.ECOG PS: The performance status of the patients before and after the completion of the whole treatment cycle according to the Eastern Cooperative Oncology Group.Quality-of-life survey: EORTC QLQ-C30 (V3.0) and EORTC QLQ-BR23 will be used to assess the QoL of patients. QLQ-C30 is a scale developed by the European Organization for Research and Treatment of Cancer (EORTC) to measure the QoL of cancer patients. QLQ-BR23 is a QoL questionnaire designed for breast cancer patients, which is suitable for evaluating all breast cancer patients regardless of the type of treatments. Also, a TCM Constitution survey based on the judgement criteria recognized by the China Association of Chinese Medicine will be conducted [28]. The TCM Constitution is assessed by filling out the “the Criteria of Classification and Judgment of TCM Constitution (ZYYXH/T157-2009)” (Table 1). Every patient is designed to respond to the questionnaire three times: (1) before chemotherapy initiation, (2) during mid-term chemotherapy, and (3) before the last cycle of chemotherapy. All assessments will be completed the day before chemotherapy administration.Survival: The differences in 3-year DFS and OS between the treatment group and the control group will be analysed.

**Table 1 Tab1:** “The Criteria of Classification and Judgment of TCM Constitution” scale

Classification	Conditions	Judgement
Normal constitution	A conversion score of ≥ 60, and conversion score of < 30 in all other 8 types	Yes
	A conversion score of ≥ 60, and conversion score of < 40 in all other 8 types	Generally yes
	Unsatisfied for the above conditions	No
Abnormal constitution	A conversion score of ≥ 40	Yes
	A conversion score of 30 to 39	Likely yes
	A conversion score of< 30	No

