#### Baseline information

Baseline information including age (below 40s, 40–60s, 60s, or above), surgical approach (breast-conserving and axillary conserving), chemotherapy regimen (anthracyclines, taxanes, anthracyclines + taxanes, and others), chemotherapy strategy (adjuvant and neoadjuvant), pathological staging (stages I, II, III), and molecular subtype (Luminal-like, HER-2 positive, and Basal-like) will be recorded.

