#### Survival analysis

The survival curve is plotted by the Kaplan-Meier Method. The log-rank test is used to compare the difference between groups.

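### Randomisation is stratified by age, regimen and strategy, but the named between-group tests leave these factors out; if the strata are balanced and prognostic, the tests are conservative and some power can be lost

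*Protocol article*

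**What the plan says.** Under Trial design {8} of the protocol article: "Patients will be divided into groups by stratified randomized grouping". It continues: "The stratification factors involve age (below 40s, 40s, 50s, 60s, or above), chemotherapy regimen (anthracyclines, taxanes, anthracyclines combined with taxane, and others", and the third factor is chemotherapy strategy, adjuvant or neoadjuvant.

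The analysis sections do not carry these factors into the group comparisons. Categorical variables: "If the data is not in order, the chi-square test or Fisher’s exact test is used to compare the difference between groups". Survival analysis: "The log-rank test is used to compare the difference between groups". The Continuous variables section likewise names one-way ANOVA or the Kruskal-Wallis test with no mention of strata. Statistical methods {20a} lists linear, Cox and logistic regression for use as the case calls for, without covariates and without saying whether such a model is primary or supportive.

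Two other passages concern the same factors. The Baseline information section gives different age bands: "Baseline information including age (below 40s, 40–60s, 60s, or above". These merge the 40s and 50s, and as printed the middle band overlaps the top one. The Secondary outcomes section promises: "Subgroup analysis will be done according to age, chemotherapy regimen, and chemotherapy strategy". The section on additional analyses {20b}, whose heading gives subgroup analyses as its example, says there are none.

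**The concern.** Balancing the arms within strata makes the estimated difference more precise than under simple randomisation, provided the strata predict outcome. A test that ignores the strata uses a standard error that does not reflect this gain. It is then conservative: the true type I error falls below 5%, and power falls below what the design could deliver. The price is a missed effect, not a false one.

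This matters most for the smaller contrasts. The Sample size section sizes the trial only for MD or MP against control, so MD v MP has no stated power of its own. The age bands and the subgroup statements also need to agree, because an adjusted or subgroup analysis by age cannot be run as planned while two bandings are in force.

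**Working it through.** **Inputs from the protocol article**
- Strata: 4 × 4 × 2 = 32 cells (Trial design {8}).
- 154 per group, 462 in total, 1:1:1, 20% dropout, α = 0.05 (Sample size {14}); two-sided tests (Statistical methods {20a}).
- Event rates: 81.0% control v 61.7% decoction (previous study); 81% control v 52% MD with a 15-point margin (preliminary study).
- Power is printed as 1−β = 0.08. It can be read as power 0.80 or, taking β = 0.08, as power 0.92.

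**Assumptions not in the documents**
- Permuted blocks of 6 within each stratum, and the mix of patients over strata.
- The share R² of outcome variance explained by the strata, from 0 to 0.18.
- A smaller effect of 81% v 66.4%. Here 66.4% is only an illustrative event rate; it is not the moxibustion effective rate that the Sample size section prints with the same value.

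**Step 1: the plan's own figure.** Two routes reach 154 or nearly so.
- Superiority by a margin, one-sided 5%, power 0.80: (0.52×0.48 + 0.81×0.19) × (1.645 + 0.842)² / (0.29 − 0.15)² = 0.4035 × 6.183 / 0.0196 = 127.3, so 128. Then 128 × 1.2 = 153.6, so 154.
- Two proportions, 81% v 61.7%, two-sided 5%, power 0.92, pooled variance under the null: 122. Then 122 / 0.8 = 152.5, so 153.

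The match is not unique, and neither route uses the strata. What the check needs is the number analysed: 154 × 0.8 = 123.2, so 123 per arm and 369 in total. That is 369 / 32 = 11.5 patients per cell, or 3.8 per arm per cell. By formula, the unstratified power at 123 per arm for 81% v 61.7% is 92.2%.

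**Step 2: analytic size of the unstratified test.** With balance within strata, the test's standard error is too large by a factor 1/√(1−R²), so the true size is 2[1 − Φ(1.96/√(1−R²))].
- R² = 0: factor 1.000, size 5.0%.
- R² = 0.025: factor 1.013, critical value 1.985, size 4.7%.
- R² = 0.093: factor 1.050, critical value 2.058, size 4.0%.
- R² = 0.183: factor 1.107, critical value 2.168, size 3.0%.

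**Step 3: simulation of control v MD within the three-arm design, 123 per arm.** Each entry is a percentage for Pearson chi-square / CMH on 32 strata / CMH on 24 strata (40s and 50s merged).

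| R² | Null rejection | Power, 81% v 61.7% | Power, 81% v 66.4% |
|---|---|---|---|
| 0 | 4.6 / 4.6 / 4.5 | not run | 74.9 / 73.8 / 73.8 |
| 0.025 | 4.8 / 4.9 / 4.9 | 92.7 / 92.4 / 92.6 | 75.0 / 74.1 / 74.2 |
| 0.093 | 4.2 / 4.9 / 4.7 | 93.0 / 93.7 / 93.9 | 75.0 / 76.3 / 76.8 |
| 0.183 | 3.1 / 5.1 / 4.9 | 93.6 / 95.6 / 95.9 | 76.9 / 82.5 / 82.9 |

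For the rows with R² above 0, the null column rests on 6,000 runs (standard error about √(0.05 × 0.95 / 6000) = 0.28 points) and the first power column on 3,000.

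**Reading the table.** At 81% v 61.7% the 32-stratum CMH test gains −0.3, 0.7 and 2.0 points over the chi-square test. At 81% v 66.4% it gains −1.1, −0.9, 1.3 and 5.6 points. Merging the 40s and 50s changes power by 0.5 points at most.

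**The case against.** The strongest reply is that the loss rests on two conditions that the documents do not establish.
- *Balance within strata.* The article describes stratified grouping with a sequence generated in SPSS, but mentions no blocking. Without balance the unstratified test keeps its size: under simple randomisation of 256 patients over 32 strata, with assumed stratum risks spread over 55–96% and 47–98%, type I error was 5.2% and 4.8%.
- *Prognostic strata.* No stratum-specific risks are given. At R² of 0 or 0.025 nothing is lost.

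Both points stand, so the consequence can only be stated conditionally. A reader might infer that the reported P values will certainly be too large, or that ignoring the strata raises the false-positive rate. The first does not follow from the documents; the second has the direction wrong.

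It can also be said that {20a} already lists regression, and that covariates and the role of a model are commonly left to a SAP. That is fair, and their absence is not the point here. The point is that the article does name its between-group tests, and those tests omit the factors used to randomise.

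A reader might infer from the three-band age variable that the randomisation strata cannot be rebuilt. That is not so: the assessment schedule (Table 3) lists age itself as a baseline item, and the stratum must be known in order to randomise.

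A reader might also infer that prophylactic rhG-CSF is the dominant determinant of neutropenia and splits the anthracycline-plus-taxane class. The rhG-CSF section says "Two types of adjuvant chemotherapy regimens in breast cancer, namely ddAC-wP and TAC, can lead to a high risk of FN", but it does not say that the other regimens in that class go without prophylaxis, and nothing in the article ranks determinants. Chance imbalance in a covariate not used for stratification is already part of the test's sampling error.

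**Conclusion.** The point holds as a modest inefficiency in a stated method. The trial randomises by three factors and then names comparisons that do not use them. Given balance within strata and R² between 0 and 0.18, the true size of the nominal 5% test runs from about 5% down to 3%. The power loss is nil to about 2 points at the article's 81% v 61.7%, and up to about 6 points at the illustrative 81% v 66.4%. These figures rest on the assumed block size, patient mix and R², and they cover a two-arm comparison of proportions only; the survival tests were not simulated.

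The conflict between the two sets of age bands, and that between the Secondary outcomes section and {20b}, are real. They are matters to reconcile and add almost nothing to the loss of power.

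**What to change.** - **Proportion outcomes.** Make the primary comparison a logistic model with treatment and the three stratification factors as main effects, and report an adjusted risk difference with 95% CI. A CMH test is an acceptable alternative. With about 3.8 analysed patients per arm per cell, main effects (3 + 3 + 1 = 7 terms) are preferable to full cross-stratification.
- **Survival.** Stratify the log-rank test or adjust a Cox model for the same factors; the sparse cells again favour main effects.
- **Role of the models.** State in {20a} that these adjusted analyses are primary and that the unadjusted tests are supportive.
- **Age.** In Baseline information, use the four randomisation bands or age in years in place of the three overlapping bands.
- **Subgroups.** Bring {20b} into line with the Secondary outcomes section by naming the three factors there, with treatment-by-factor interaction tests, or by withdrawing the promise.
- **Optional.** Planned prophylactic rhG-CSF may be added as a covariate.

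The cost is wording in the analysis plan and the case report form; age, regimen and strategy are already baseline items in Table 3. If the strata turn out not to be prognostic, the price is about 1 point of power at most. That was seen for the 32-cell CMH test; the main-effects model was not simulated separately.
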